### Sample Size Calculation

The sample size is calculated using G^*^Power 3.1.9.4 (University of Kiel) for the expected results of physical performance (6MWT) and mental well-being (depression). While 6MWT is a standardized measurement to assess physical capacity in patients with chronic disease during rehabilitation, e.g., COPD, (87–89) it was used as the primary outcome of physical performance for sample size calculation. 6MWT was also conducted in the first inpatient rehabilitation studies with patients with COVID-19 and showed good feasibility (31, 55). Multiple regression analyses assess the baseline situation of patients after acute COVID-19 with regard to physical resilience or mental health at the beginning of the inpatient rehabilitation. Due to the novelty of the disease, there are no representative comparative values for associations between COVID-19 and physical resilience and mental health. Therefore, the calculation of sample size in the cross-sectional analysis refers to the generic effect size measure *f*^2^. According to Cohen (97), a mean effect size of *f*^2^ = 0.15 will be used to calculate the sample size. Results from studies on correlations in patients with pneumological diseases (e.g., COPD) are used to justify this selected effect size in more detail. The study by Zeng et al. (98) identified age, severity of disease, and quality of life as significant predictors for physical performance measured by 6-minute-walking-distance in patients with COPD with a medium effect size of *f*^2^ = 0.21. In a regression model, von Leupoldt et al. (99) showed that depression is one out of 6 predictors (e.g., age, gender, forced expiratory volume in 1 s) for the completed 6MWT in COPD-patients in outpatient rehabilitation with a small effect size of *f*^2^ = 0.06 (71). Due to the heterogeneity of study results, a medium effect size of *f*^2^ = 0.15 can be assumed for the calculation of sample size to present associations between physical performance and mental health. With a planned power of 80% and significance level of 5%, 92 data sets are required, considering up to 5 potential predictors (e.g., pulmonary function values, blood gas values, age).

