To detect the outcomes over time, differences between 2 dependent samples (T1 and T2) will be analyzed. The minimal clinically important difference between two measurement time points is 30 meters for the 6-minute-walking-distance (88). According to experience from our own studies on physical performance in patients with occupational respiratory diseases, standard deviations between 80 and 100 m are to be expected (100, 101). Assuming a standard deviation of 100 m (due to heterogeneity of the sample) and an expected effect size of d = 0.3, 71 data sets are required with a power of 80% and significance level of 5%.

While a drop-out rate of 25% is expected during the study period of 21 months, a total sample size of at least 115 patients will be included.

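### The 25% drop-out allowance appears to have been applied as 92 × 1.25 = 115; at that rate 115 enrolled patients leave about 86 data sets, not the 92 required

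*Protocol article*

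**What the plan says.** All statements are in the protocol article, Sample Size Calculation.

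- **Regression.** The requirement is: "With a planned power of 80% and significance level of 5%, 92 data sets are required, considering up to 5 potential predictors". The effect size behind it is given as "a medium effect size of *f*^2^ = 0.15 can be assumed for the calculation of sample size". The section places this analysis at the start of rehabilitation: "Multiple regression analyses assess the baseline situation of patients after acute COVID-19". It also calls it cross-sectional: "the calculation of sample size in the cross-sectional analysis refers to the generic effect size measure".
- **Change over time.** For the 6-minute walk distance, "differences between 2 dependent samples (T1 and T2) will be analyzed". With d = 0.3, 80% power and a 5% level, the stated requirement is 71 data sets.
- **Drop-out and total.** The enrolment target reads: "While a drop-out rate of 25% is expected during the study period of 21 months, a total sample size of at least 115 patients".

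The larger of the two requirements is 92. The section does not show how it gets from there to 115, and it does not say which of the two analyses the allowance is meant to protect.

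**The concern.** A drop-out rate is a share of the patients enrolled. To keep n after a loss of share d, one enrols n / (1 − d). Multiplying n by (1 + d) takes the share of the smaller number, and the result is always too low. The stated total equals the second calculation exactly.

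If so, the enrolment target does not do the one thing an allowance is for: at the protocol's own drop-out rate it does not leave the 92 data sets that the protocol asks for. What is at stake is the accuracy of the sample size statement and the power of any regression of this kind run on patients still present at follow-up. Such regressions are planned. The research questions at the end of the Introduction ask about predictors of long-term outcomes and of return to work, and the Statistical Analysis section plans regressions on long-term outcomes. No separate sample size is given for them.

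**Working it through.** **Inputs, all from Sample Size Calculation:** f² = 0.15, 5 predictors, alpha 5%, power 80%, 92 data sets (regression); d = 0.3, 71 data sets (paired T1–T2 comparison); drop-out 25%; total at least 115.

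**1. Reproduce the 92.** Overall F test of a multiple regression with p = 5 predictors, noncentrality λ = f² × N, degrees of freedom 5 and N − 6:

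- N = 91: power 79.9%
- N = 92: λ = 0.15 × 92 = 13.8, df = 5 and 86, power 80.4%

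The smallest N that reaches 80% is 92, as stated.

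**2. Find the step to 115.**

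| Starting figure | n × 1.25 | n / 0.75 |
|---|---|---|
| 92 | 115.0 | 122.7, so 123 |
| 71 | 88.75, so 89 | 94.7, so 95 |

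Only 92 × 1.25 gives 115.

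**3. What 115 leaves.**

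- At 25% drop-out: 115 × 0.75 = 86.25, about 86. Shortfall: 92 − 86 = 6.
- Drop-out at which 92 remain: 1 − 92/115 = 0.20.
- Enrolment that keeps 92 at 25% drop-out: 123, which is 8 more than 115.

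**4. Power by analysis.**

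| Analysis | N | Power |
|---|---|---|
| T1 regression, all 115 give T1 data | 115 (λ = 17.25, df 5 and 109) | 89.9% |
| Regression at the required size | 92 (λ = 13.8, df 5 and 86) | 80.4% |
| Same linear regression after 25% loss, e.g. at T3 or T4 | 86 (λ = 12.9, df 5 and 80) | 77.0% |

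The difference between the last two rows is 80.4 − 77.0 = 3.4 percentage points.

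For the T1–T2 comparison, 86 exceeds the stated 71. On that figure 115 tolerates a loss of 1 − 71/115 = 38%. The 71 reproduces with a one-sided paired t test (power 80.5% at 71), and on that basis 86 pairs give 86.8%.

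**The case against.** The strongest reply is that drop-out hardly touches the analysis that produced 92. The section describes that regression as cross-sectional and as concerning the baseline situation. Losses over 21 months arise mostly after T1, and with T1 data from all 115 patients the power is about 90%. The T1–T2 comparison is covered by its stated 71. A reader might infer from the shortfall that the trial as a whole does not deliver its 80% power. The document does not support that: on its own figures, neither of the two analyses it sized is shown to fall below 80% because of this slip. Nor does the text promise 80% power for a regression after 25% drop-out.

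The move to follow-up is also conditional. The Statistical Analysis section leaves the regressions on long-term outcomes open, and its one worked example is logistic (return to work at 6 or 12 months). The F test with f² = 0.15 does not size a logistic model, and no power is stated for any regression at T3 or T4. The 77% therefore holds only for a linear five-predictor model on those left after the full loss.

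These points limit the consequence, and they stand. They do not remove the arithmetic error. If the allowance was not meant for the 92, there was no reason to inflate 92: 71 with a correct allowance needs only 95. The figure 115 makes sense only as an attempt to keep 92 after 25% loss, and it does not keep them. That 115 is a minimum does not help either, because the minimum is the number that should meet the requirement.

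One caution on the paired comparison: with a two-sided test the requirement would be 90, not 71, and 86 pairs would give 78.5%. The section does not state the sidedness. That is a separate matter, and this point does not rest on it.

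**Conclusion.** The concern holds as an inconsistency between the stated drop-out rate, the required number of data sets and the total. At 25% drop-out, 115 enrolled patients leave about 86 data sets, 6 fewer than 92. The total is right for 20% drop-out, and 123 would be right for 25%.

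The effect on power is limited to a linear five-predictor regression run on the patients remaining after the full 25% loss: about 77% instead of 80%, assuming f² = 0.15, alpha 5% and no enrolment beyond 115. That the total was reached as 92 × 1.25 is an inference from an exact match, because the step is not printed. The shortfall of 6 does not depend on that inference.

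This is a minor correction. The effect size is itself generic: the section cites values of 0.06 and 0.21 on either side of 0.15, and against that uncertainty a loss of 3.4 points is small.

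**What to change.** In the last paragraph of Sample Size Calculation, name the analysis that the drop-out allowance protects, and restate the figure. Suggested wording:

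> 115 enrolled patients leave about 86 data sets at 25% drop-out, giving about 77% power for a five-predictor linear regression at follow-up (f² = 0.15, alpha 5%). The required 92 data sets are retained only if drop-out is at most 20%; at 25% drop-out, 123 enrolled patients would be needed. The baseline regression has about 90% power if all 115 patients provide T1 data.

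The power statement should stay tied to the named analysis. A general statement that 80% power requires drop-out of at most 20% would be untrue for the T1 regression with complete T1 data, and untrue for the T1–T2 comparison on its stated 71.

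The cost is a short rewording and a slightly less favourable power figure for follow-up regressions. No extra patients are needed if the figure is restated. Keeping 92 data sets at 25% drop-out would take 123 − 115 = 8 more.

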### Statistical Analysis

IBM SPSS Statistics Version 28 and AMOS Version 28 (IBM Corp., Armork, NY, USA) will be used for all statistical analyses.

First, to determine the existing outcomes of COVID-19 on physical capacity, psychological and cognitive well-being, and the ability to work at the beginning of inpatient rehabilitation (T1), the population will be descriptively characterized by all measured outcomes. Data from participants at the end of inpatient rehabilitation (T2) and at the follow-up time points (T3, T4) will be analyzed to further evaluate the long-term outcomes of patients with COVID-19 undergoing an intensive rehabilitation in terms of physical capacity, psychological and cognitive well-being, and the ability to work. Normal distribution and homoscedasticity of the sample will be realized using the paired *T*-test or Wilcoxon-test. Depending on the feasibility for the current population, group differences (e.g., age, gender, pre-existing conditions, comorbidities, current employment) in the long-term effects of COVID-19 on physical capacity, psychological and cognitive well-being, and the ability to work will be analyzed separately for the different time points (T1, T2, T3, T4) using different statistical methods as follows. Taking into account the number and size of groups, normal distribution and homoscedasticity of the sample, parametric or non-parametric statistical methods such as the *T*-test, Mann-Whitney *U*-test, ANOVA, or the Kruskal Wallis test will be used. To evaluate the associations between the different outcome measures of physical capacity, psychological and cognitive well-being, and ability to work, correlation analysis will be performed to measure the strength of the relationship between two variables, e.g., 6MGT and HADS-D or 6MGT and WAI. Depending on these results and current insights from the literature, multivariate and logistic regression analyses accounting for confounders such as age, gender, or comorbidities will be conducted to identify predictors or meditators of the long-term outcomes of COVID-19. For example, a logistic regression analysis will be used to examine the relationship between physical capacity, psychological and cognitive well-being and the dependent variable return to work 6 or 12 months after the start of inpatient rehabilitation. For all analyses, Bonferroni correction for multiple testing will be applied and statistical significance level will be set to *p* < 0.05. After inspecting the amount and pattern of missing data and outlier values, the most appropriate procedure for addressing both factors will be selected.

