
In summary, rehabilitation programs can contribute to a reduction in physical, neurocognitive, and psychological restrictions, thereby stabilizing or even increasing patients' physical and mental performance after recovery from COVID-19. This is a prerequisite for maintaining the ability to work on a long-term basis after COVID-19, which is associated with economic costs. Considering the diverse and variable symptomatology, especially the associated physical limitations, social and occupational participation disorders are to be expected. However, there is currently no research focusing on the nature and extent of returning to work after COVID-19. Consequently, COVID-19 is associated with great challenges for the healthcare systems worldwide. In addition to acute patient treatment, long-term care of COVID-19 patients will be necessary after the acute phase due to illness-related impairments. However, based on the lack of longitudinal data and results, the sustainability of rehabilitation effects could not yet be confirmed. Indeed, since patients with severe to critical COVID-19 seem to benefit from rehabilitation soon after the acute phase of infection, rehabilitation programs are recommended for all hospitalized COVID-19 patients to avoid long-term adverse health outcomes (53, 60). However, inpatient rehabilitation programs should not only be offered directly after hospitalization and temporary discharge, but also weeks and months after the acute phase of COVID-19, depending on the existing symptoms of post-COVID (51). Together with the case control management of health services, rehabilitation should be provided to regain functionality in everyday and workday activities.

In this context, this study examines the following main research questions:

- What are the long-term outcomes of patients following OAC after undergoing an intensive rehabilitation program? Of particular interest are patients' physical capacity, psychological and cognitive well-being, and ability to work.- Are age, gender, previous diseases, and employment at the time of exposure, as well as comorbidities associated with long-term outcomes of OAC of patients' physical capacity, psychological and cognitive well-being, and ability to work?- Are physical capacity and psychological and/or cognitive well-being predictors for ability to work or return-to-work?

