### Participants

Based on the admission lists for rehabilitation after acute COVID-19 at the BG Hospital for Occupational Disease Bad Reichenhall, all patients concerned will be contacted by a trained study nurse from the clinic to inform them about the aims and the procedure of the current study in a standardized telephone interview. If patients agree to receive more information about the study, they will be sent written informed consent forms, the declaration of data protection, and the first assessments (T1) by mail.

Eligibility for study participation will be determined by the following inclusion criteria, regardless of age, gender, and migrant background: (1) COVID-19 as a recognized occupational disease or work-related accident, (2) patients in the post-acute phase of mild, moderate, severe, or critical COVID-19 as defined by the WHO, (3) no evidence of acute infectivity with SARS-CoV-2, (4) confirmation of coverage of costs for rehabilitation by the statutory accident insurers or the employers' liability insurance association responsible for the patient, and (5) voluntary participation. Participants will be excluded from the study if they were diagnosed with severe cardiovascular, respiratory, neurological, or musculoskeletal disorders, as well as mental (e.g., major depression) or neurocognitive (e.g., dementia) disorders prior to their infection with COVID-19.

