
#### Measurements to Assess Work Ability

Employment status and ability to work will be assessed using the following questionnaires: the Work Ability Index [WAI; (83)] as primary outcome in this area of the investigation, the Brief Scale for Measuring Subjective Prognosis of Gainful Employment [SPE-Scale; (84)], and the History of work ability and employment after acute COVID-19 [in comparison to DEGS; (71)] (see also Table 1). These questionnaires assess functional recovery in terms of work ability and employment (e.g., days from diagnosis to first partial/complete return to previous work, work interruptions due to sick leave) for the subsequent period up to 12 months after the start of inpatient rehabilitation. Additionally, physicians will record detailed information during medical anamnesis.

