#### Questionnaire Battery

The participants will complete a questionnaire battery at all measurements. The questionnaire battery will include the following outcome parameters: socio-economic status, quality of life, work ability and employment. The self-administered questionnaire includes validated instruments and self-generated items (see Table 1).

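### Research question 2 asks about employment at exposure, but the only employment grouping factor the analysis names is current employment, a post-infection status that belongs to the work outcome

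*Protocol article*

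**What the plan says.** Among the main research questions at the end of the Introduction, the second reads "Are age, gender, previous diseases, and employment at the time of exposure, as well as comorbidities associated with long-term outcomes of OAC", the outcomes being physical capacity, psychological and cognitive well-being, and ability to work.

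The Statistical Analysis section takes up this question by planning to examine "group differences (e.g., age, gender, pre-existing conditions, comorbidities, current employment) in the long-term effects of COVID-19" on the same outcome domains. These differences "will be analyzed separately for the different time points (T1, T2, T3, T4"). The list is given as examples, and the comparison depends on what proves feasible in the population.

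The Conclusion promises results on the influence of age, gender, comorbidities and a third term, occupation.

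Employment is also an outcome. Measurements to Assess Work Ability states "Employment status and ability to work will be assessed using the following questionnaires", and then "These questionnaires assess functional recovery in terms of work ability and employment". Questionnaire Battery says "The questionnaire battery will include the following outcome parameters: socio-economic status, quality of life, work ability and employment", and that "The participants will complete a questionnaire battery at all measurements". The planned logistic regression has return to work at 6 or 12 months as its dependent variable.

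**The concern.** The research question names a factor fixed before the disease course begins. The analysis names one that the disease can change. A patient who recovers poorly may reduce hours, change jobs or stop working, and so fall into a different current-employment group because of the outcome being compared. A difference between such groups can arise even if the job held at infection has no bearing on recovery.

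At stake is the answer to a main research question. The Conclusion announces findings on the influence of occupation and says results will be presented to the accident insurance institutions. A contrast produced by poor recovery could then be reported as an effect of the job.

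**Working it through.** The plan states no figure on this point, so the main check is a comparison of its own statements.

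**1. The two lists**

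| Research question 2 (Introduction) | Grouping factors (Statistical Analysis) |
|---|---|
| age | age |
| gender | gender |
| previous diseases | pre-existing conditions |
| comorbidities | comorbidities |
| employment at exposure | current employment |

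Four of the five items correspond. Only employment changes in meaning. Nothing in the article equates the two terms.

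**2. Timing.** Under Participants, eligible people are "patients in the post-acute phase of mild, moderate, severe, or critical COVID-19 as defined by the WHO". The first measurement is at the start of rehabilitation, so current employment follows infection at every visit, T1 included.

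**3. Role.** Measurements to Assess Work Ability and Questionnaire Battery both place employment among the outcomes.
- For the Work Ability Index (WAI) and return to work, grouping by current employment relates one part of the work outcome to another.
- For the 6-Minute Walk Test, mood, fatigue or cognition there is no such overlap. The issue there is the direction of effect: poorer health may alter employment.

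**4. Plausibility.** The Introduction cites a cohort in which 45.2% of patients cut their working hours and 22.3% were unable to work because of symptoms up to 6 months after acute COVID-19. These are not job-loss rates, but they show work status moving with health during the follow-up window.

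**5. Illustrative size (every input assumed).** Suppose a share p is no longer employed at T4, job loss falls on those lowest on a normally distributed health trait, that trait correlates r with the WAI, and occupation at infection has no effect. The expected difference in WAI between current-employment groups, in SD units, is

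gap = r × φ(z_p) / [p(1 − p)].

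- p = 0.15: φ(z_p) = 0.233 and p(1 − p) = 0.1275, ratio 1.83. The gap is 0.55 for r = 0.3 and 0.91 for r = 0.5.
- p = 0.30: φ(z_p) = 0.348 and p(1 − p) = 0.21, ratio 1.66. The gap is 0.50 for r = 0.3 and 0.83 for r = 0.5.

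**6. Simulation (also assumed).** This used n = 92 (the plan's regression sample size), 2,000 runs, a two-sided t-test at 5%, a pre-infection factor unrelated to a standardised outcome, and current employment depending on that outcome, with about half the sample employed.

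| Log-odds of employment per SD of outcome | Rejection rate, pre-infection factor | Rejection rate, current employment | Mean apparent gap, current employment |
|---|---|---|---|
| 0.3 | 4.9% | 29% | 0.30 SD |
| 0.5 | 5.0% | 65% | 0.48 SD |
| 1.0 | 4.4% | 99% | 0.82 SD |

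The pre-infection factor holds its nominal error rate; the post-infection status does not.

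**The case against.** The strongest defence is that the wording is loose rather than wrong. The list is offered as examples and made conditional on feasibility, so employment at exposure is not excluded. The planned regressions leave their predictor set open. Current employment may simply mean the type of job held, as the Conclusion's occupation suggests. Read that way at T1, it would match employment at exposure except for patients who changed jobs between infection and T1, a number the documents do not give. A descriptive comparison by current employment is also legitimate in an observational cohort.

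Much of this stands, and it rules out three stronger readings:
- A reader might infer that research question 2 will go unanswered. The text does not establish this, because a list of examples does not rule out the right variable.
- A reader might infer that patients are re-grouped at each visit. The plan says that group differences are analysed separately by time point, not that group membership is re-read. Repeated questioning makes re-grouping possible; it does not specify it.
- A reader might call every such comparison circular. True overlap applies only to the work outcomes.

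The defence does not remove the mismatch. Employment at exposure is named in a main research question, and the only employment grouping factor named in the analysis is a different variable. Read once at T1, it would still post-date infection. Three terms for one factor leave the choice open until the data are seen.

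**Conclusion.** The point holds as a mismatch between research question and analysis. Followed literally, the Statistical Analysis section would address a main question with a variable measured after infection that belongs to the work outcome. The result would overlap with the outcome for work ability and return to work, and be open to reverse causation for the physical, psychological and cognitive outcomes. The risk is greatest if status is read at T3 or T4.

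The size of any bias cannot be derived from the documents. The range of 0.50 to 0.91 SD depends on the assumed job-loss shares, the assumed correlations, a two-group split into employed and not employed, and a true occupational effect set to zero. That the gap is entirely spurious is true by construction, so it should not be quoted as an expected bias. The correction should be made, because it is cheap and bears on a main research question.

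**What to change.** In Statistical Analysis, replace current employment in the list of grouping factors with *employment (occupation/sector) at the time of exposure*, recorded once at T1 and held fixed for the comparisons at T1 to T4. Use the same term in the Conclusion.

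Treat current employment at follow-up as an outcome. If a comparison by current employment is still wanted, label it descriptive and do not report it as an influence of occupation.

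The cost is one wording change and at most one retrospective item in the T1 questionnaire. The information should be obtainable, since recognition as an occupational disease or work-related accident rests on the insured activity and is an inclusion criterion. No extra visit or patient is needed.

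### The planned test of age as a factor compares groups, so age would have to be cut into classes; a continuous age term would keep the lost power at almost no cost

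*Protocol article*

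**What the plan says.** The research questions at the end of the Introduction include: "Are age, gender, previous diseases, and employment at the time of exposure, as well as comorbidities associated with long-term outcomes of OAC".

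The Statistical Analysis section takes this up as "group differences (e.g., age, gender, pre-existing conditions, comorbidities, current employment) in the long-term effects of COVID-19", to be examined separately at T1, T2, T3 and T4 as far as feasible. On method it says that, in view of the number and size of groups and of distributional checks, "parametric or non-parametric statistical methods such as the *T*-test, Mann-Whitney *U*-test, ANOVA, or the Kruskal Wallis test will be used". No age classes or cut points are given.

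Age appears in two other places:
- Later in the same section, in models meant to explain how patients fare in the long term: "multivariate and logistic regression analyses accounting for confounders such as age, gender, or comorbidities will be conducted to identify predictors or meditators". These models are introduced with "Depending on these results and current insights from the literature".
- In Sample Size Calculation, a multiple regression is sized "considering up to 5 potential predictors (e.g., pulmonary function values, blood gas values, age"). That regression describes the situation at the start of rehabilitation (T1).

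**The concern.** Age is measured in years, and the question is one of association. Each of the four named tests compares groups and can use age only after it has been cut into classes. Cutting discards the differences within classes, so a real age gradient in walking distance, MoCA, WAI or the psychological scores at T3 or T4 is more likely to be missed. The result also comes to depend on where the cut falls.

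The group comparison is the only analysis in that section that treats age as the factor of interest. The correlation analysis covers relations between outcome measures, and age is not one of them. The sample-size regression concerns T1. In the later regressions age is an adjustment variable, and the worked example relates capacity and well-being to return to work. A cohort of about 115 patients has little information to spare.

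**Working it through.** **1. The plan's own figure.** Inputs from Sample Size Calculation: "a medium effect size of *f*^2^ = 0.15 can be assumed for the calculation of sample size", five predictors, and "With a planned power of 80% and significance level of 5%, 92 data sets are required". The overall F test with noncentrality λ = N·f² and 5 and N − 6 degrees of freedom gives N = 92 with power 0.804. The stated figure is reproduced. It covers the whole five-predictor model; no power is stated for age or for any group comparison.

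**2. Inputs for age.**
- N = 92 (required data sets), 115 (planned enrolment) and 86 (115 × 0.75 = 86.25, after the expected 25% drop-out).
- f² for age alone: not in the documents. As an assumed range I take the two ends 0.15 (the plan's value for the whole model) and 0.06 (the small effect cited from a six-predictor regression in COPD).
- Further assumptions: age roughly normal, association linear, two-sided 5% level without correction.

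**3. Variance kept after cutting.** For normal age:
- median split: 2/π = 0.637, a loss of about 36%;
- thirds: the outer class means lie at ±1.091 SD, so (2/3) × 1.091² = 0.793, a loss of about 21%.

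**4. Power.** With R² = f²/(1 + f²) and a fraction e retained, R²c = e·R² and λ = N·R²c/(1 − R²c), with k − 1 and N − k degrees of freedom for k classes. For continuous age, e = 1 with 1 and N − 2 degrees of freedom.

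Example, N = 92 and f² = 0.15: R² = 0.130.
- Continuous: λ = 92 × 0.15 = 13.8, power 95.7%.
- Median split: R²c = 0.637 × 0.130 = 0.083, λ = 92 × 0.083/0.917 = 8.3, power 81.5%.

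| N | f² | Continuous | Median split (loss) | Thirds (loss) |
|---|---|---|---|---|
| 86 | 0.15 | 94.4% | 78.8% (15.6) | 79.7% (14.7) |
| 86 | 0.06 | 61.2% | 42.6% (18.7) | 40.6% (20.6) |
| 92 | 0.15 | 95.7% | 81.5% (14.2) | 82.6% (13.1) |
| 92 | 0.06 | 64.2% | 45.0% (19.2) | 43.2% (21.0) |
| 115 | 0.15 | 98.5% | 89.2% (9.2) | 90.6% (7.8) |
| 115 | 0.06 | 74.0% | 53.8% (20.2) | 52.6% (21.5) |

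Losses are in percentage points, from unrounded powers. At r = 0.30, between the two ends, they are 17 to 21 points. A simulation of 40,000 bivariate normal data sets per cell at N = 92 agrees to within about one point: 94.7 / 81.0 / 81.5% at f² = 0.15 and 63.0 / 44.6 / 42.9% at f² = 0.06.

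**5. Uneven cuts.** In the same simulation an upper-quarter cut gives 73.2% at f² = 0.15 (loss 21.5) and 38.7% at f² = 0.06 (loss 24.3). At an intermediate f² = 0.10 it gives 56.9% against 84.1% (loss 27.2).

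**6. Bonferroni.** The section applies the correction to all analyses without giving the number of tests. For an assumed 4, 16 or 20 tests, over the same N and f² and for a median split or thirds, the loss runs from about 11 to 31 points. At N = 92 and f² = 0.15 with 4 tests, continuous age has 87.5% power and a median split loses 24.3 points. At f² = 0.06 with 20 tests, continuous age has 23.2% and the split loses 12.0.

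**The case against.** The strongest reply is that the group tests are not the only route to the age question. The later regressions aim to identify predictors of the long-term outcomes and contain age, and nothing says it is categorised there. They depend on the literature as well as on earlier results, so a non-significant group test does not by itself remove age. This stands in part. A reader might infer that the research question on age itself loses the power shown above; the documents do not support that, because a regression with continuous age may be run. They do not commit to one either.

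Second, the wording is illustrative: the factors are examples, and so are the methods. That too is fair, but the frame is group differences and every named method compares groups. The point is therefore about the method indicated, not about missing cut points, which a condensed article may leave to the full protocol.

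Third, a reader might infer that classes will be formed after seeing the data. The text does not say so: the number and size of groups govern the choice of test, not how age is divided. The Introduction does mention age above 50 years, but as a predictor of a severe or critical course, and the analysis section does not adopt it as a cut.

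Finally, this is an exploratory association in a single-arm observational cohort that was not powered for group comparisons. That limits the weight of the point.

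**Conclusion.** The point holds in limited form. The analysis that treats age as a factor of interest would need age in classes, and a continuous test is possible elsewhere in the plan but not assured. For a median split or thirds, the group test loses roughly 8 to 22 points of power over N = 86 to 115 and f² = 0.06 to 0.15 at an uncorrected 5% level; an upper-quarter cut loses more.

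These figures rest on normal age, a linear association and an assumed effect size for age. A reader might be tempted to quote a single narrow loss, such as 13 to 21 points. That describes only N = 92 with a median split or thirds and no correction. At N = 115 and f² = 0.15 the loss is 8 to 9 points, and Bonferroni changes it again. Severity is minor: nothing in the study is invalidated.

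**What to change.** In Statistical Analysis, remove age from the list of group comparisons. State that its association with the T3 and T4 outcomes (6MWT, MoCA, WAI and the psychological scores) is tested with age in years as a continuous regression term, or by Spearman correlation if the assumptions fail. Add a quadratic or spline term as a check for curvature. Keep the group tests for the categorical factors, such as gender, presence of a pre-existing condition and employment category, and show age classes only descriptively.

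The cost is about one sentence, with no extra patients or data. The small downside is that a linear term can miss a threshold pattern; the curvature check addresses this.
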